### Secondary Outcomes

The overall framework of this study recognizes that substance use and sexual risk behaviors are primary drivers of HIV and other STIs, which will be assessed through self-reported data on sexual risk, substance use, and self-reported HIV and STI diagnosis, verified through independent medical chart review when submitted by participants. Intimate partner violence, stigma, sociodemographic factors, and use of web-based venues for sex or drug seeking are potential risk factors for HIV and other STIs [63-66]. PrEP use, vaccination, and condom use are potential health protective behaviors. For all participants, we posit that YMHP can also help participants make positive changes toward their self-defined substance use and sexual health goals. For participants in the uTECH+YMHP condition, uTECH can improve participants’ skills and motivation to make behavioral changes to improve their health, which may lessen their risk of acquiring HIV and other STIs. In addition, we posit that in this combined condition, positive behavior changes may be more sustainable and durable compared to receiving YMHP without uTECH.

### Assessment Measures (Baseline and 3-, 6-, 9-, and 12-Month Time Points)

This study will include 3 types of assessment: interviews, web-based surveys, and HIV risk assessments. Interviews (approximately 30 min to 1 h) will be completed at baseline and at 6-month and 12-month time points. Self-completed web-based surveys (approximately 15-30 min) will be completed at 3-month and 9-month time points. HIV risk assessment surveys (approximately 5 min) will be completed at all 5 time points (Table 2).

**Table 2 table2:** Primary and secondary outcomes of the study.

Outcomes			Measures		Variables
**Primary**					
	Acceptability, appropriateness, and feasibility of uTECH SMS text messages	Adapted from AIM^a^, IAM^b^, and FIM^c^ [65]		5-item Likert scale	
	Acceptability, appropriateness, and feasibility of Young Men’s Health Project	Adapted from AIM, IAM, and FIM [65]		5-item Likert scale	
**Secondary**					
	Sociodemographic	Multiple items		Nominal	
	Sexual risk behavior	Multiple items		Nominal, continuous, and dichotomous	
	Intimate partner violence	Intimate partner violence among gay and bisexual men scale [67]		Ordinal	
	PrEP^d^ and PEP^e^ use	Self-reported PrEP or PEP use history		Nominal, continuous; dichotomous, and 6-item Likert scale	
	STDs^f^	Self-reported STD diagnosis history		Nominal, integer, dichotomous, and interval	
	PrEP stigma	PrEP Stigma Scale [68]		5-item Likert scale	
	Substance use	The Alcohol, Smoking, and Substance Involvement Screening Test [69]		Nominal, dichotomous, and yes or no for specific substances	
	COVID-19	Self-reported COVID-19 diagnosis; how COVID-19 has impacted sexual behavior		Dichotomous and qualitative	
	Mpox (monkeypox)	Vaccination status, history of mpox diagnosis and exposure, perceived risk, and stigma		Dichotomous, nominal, interval, and 5-item Likert scale	
	Vaccine confidence	Vaccine Confidence Index [70]		5-item Likert scale	
	Vaccination history	Self-reported vaccination status for hepatitis A, hepatitis B, human papillomavirus, meningococcal B, meningococcal A, C, W, or Y, and COVID-19		Dichotomous and yes or no for specific vaccines	
	Seeking sex or drugs on social networks	Websites, chat rooms, message boards, and apps used to meet partners for sex or partying		Nominal	
	eWellness app features	Types of features (ie, notifications and device functions) and frequency or time of day of notifications that participant would be comfortable with		Nominal, 6-item Likert scale, and dichotomous	
	HIV risk assessment	Men who have sex with men risk index [71] and people who inject drug (injection drug user) risk index [72]		Nominal and ordinal	

^a^AIM: Acceptability of Intervention Measure.

^b^IAM: Intervention Appropriateness Measure.

^c^FIM: Feasibility of Intervention Measure.

^d^PrEP: pre-exposure prophylaxis.

^e^PEP: postexposure prophylaxis.

^f^STD: sexually transmitted disease.

### Expected Timeline

Development of the initial version of eWellness was completed in October 2020, and enrollment for the trial started soon after. The eWellness app continued to undergo refinement and development until phase 2 began in November 2021. Enrollment will continue until the target sample size is reached, with 12 months of study engagement per participant. We expect to complete data collection 12 months after the last participant has been enrolled in the study, that is, by June 2024, and plan the dissemination of results subsequently.

### Statistical Analyses

Statistical methods, models, and procedures will be selected according to the research hypotheses being tested and the types of measures involved. We will set α<.05 as the level for statistical significance but will use appropriate corrections for multiple comparisons (eg, Bonferroni and Hochberg correction [73]) to ensure that the actual overall effective type 1 error remains at an α=.05 level for the tests to be conducted. The frequency and patterns of missing data will be carefully evaluated. To avoid potential bias resulting from missing data, imputation (eg, hot deck or multiple imputation [74]) will be conducted, and statistical significance tests and modeling will be conducted with and without the imputed values. The findings from these analyses will be compared, and any differences will be evaluated. Potential nonlinear relationships between continuous predictors (eg, participants’ age) and outcomes (eg, acceptability, appropriateness, and feasibility of uTECH and YMHP) will be evaluated through spline functions (eg, cubic spline).

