**Methods:**

In a study funded by the National Institutes of Health, we will recruit and enroll SGM participants (aged 18-29 years) in the United States (N=330) to participate in a 12-month, 2-arm randomized comparison trial. All participants will receive 4 counseling sessions conducted over Zoom (Zoom Video Communications, Inc) with a master’s-level social worker. Participants in the uTECH+YMHP condition will receive curated SMS text messages informed by an ML algorithm that seek to promote HIV and substance use risk reduction strategies as well as undergoing YMHP counseling. We hypothesize that the uTECH+YMHP intervention will be considered acceptable, appropriate, and feasible to most participants. We also hypothesize that participants in the combined condition will experience enhanced and more durable reductions in substance use and sexual risk behaviors compared to participants receiving YMHP alone. Appropriate statistical methods, models, and procedures will be selected to evaluate primary hypotheses and behavioral health outcomes in both intervention conditions using an α<.05 significance level, including comparison tests, tests of fixed effects, and growth curve modeling.

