### Primary Outcomes

The primary outcomes that the study will measure are the acceptability, appropriateness, and feasibility of the implementation for uTECH+YMHP and YMHP-only conditions. These primary outcomes will be assessed through surveys conducted at 3-, 6-, 9-, and 12-month time points. The study will measure how outcomes differ between uTECH+YMHP and YMHP-only conditions.

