### Planned Analytic Approach

Primary outcomes for the study include the acceptability, appropriateness, and feasibility of each intervention condition. In addition, we will examine behavioral health outcomes (sexual risk and protective behaviors and substance use) in both intervention conditions. Tests of fixed effects for estimates of time-specific differences will be performed using appropriate contrasts. Trend changes and their significance will be analyzed, driven by variance components (random effects). We will use growth curve modeling [75] to examine the effects of treatment on outcomes. Growth curve factors also account for the covariation of follow-up observations within participants. Data from 3-, 6-, 9-, and 12-month follow-up assessments will be modeled using latent growth factors using R statistical software [76] (version 4.4.0; R Foundation for Statistical Computing). Because the first nonbaseline time point in the latent growth curve will be the 3-month follow-up, significant differences in the intercept factor would indicate significant postintervention effects. Significant differences in slope factors would indicate that the groups follow different trajectories. When this is noted, potential group differences at each follow-up assessment will be evaluated by varying the location of the referent time point.

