### Sample Size Calculation and Power Analysis

For the power calculation, we used 1 primary outcome, acceptability. We used a balanced repeated measures design [84] with pretreatment baseline measurements. Using a logistic regression generalized linear mixed model [85], we allowed an individual’s 5 measurements (baseline and 3-, 6-, 9-, and 12-month) for acceptability to be correlated via an autoregressive-1 structure. With an initial sample size of 330 (to account for 95% retention), an autocorrelation of 0.1, and a baseline effectiveness of 85%, we aimed to detect a minimum time-averaged difference of 9% in acceptability between any 2 conditions, maintaining 80% power and an a priori α level of .05. This calculation was based on pairwise comparisons between uTECH+YMHP versus YMHP-only conditions. If the autocorrelation [86] between measures within the same individual was as high as 0.5, the sample size was adjusted to detect a minimum difference of 11% between the 2 conditions. A 9% to 11% difference between the 2 conditions is considered statistically significant, given the existing evidence supporting YMHP and the relative cost-effectiveness and ease of delivery of the uTECH intervention. The ability to demonstrate a small increase in the acceptability of uTECH over YMHP will support the widespread implementation of uTECH in future efficacy trials.

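### The stated 80% power is for a time-averaged acceptability difference at an uncorrected .05, which is not one of the tests planned for the three primary outcomes

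*Protocol article*

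**What the plan says.** - **Primary Outcomes** gives three outcomes without ranking them: "The primary outcomes that the study will measure are the acceptability, appropriateness, and feasibility of the implementation for uTECH+YMHP and YMHP-only conditions". They are assessed at 3, 6, 9 and 12 months.
- **Statistical Analyses** sets .05 and then applies corrections, with Bonferroni and Hochberg as examples, "to ensure that the actual overall effective type 1 error remains at an α=.05 level for the tests to be conducted".
- **Planned Analytic Approach** fits growth curves to months 3 to 12. On the intercept: "significant differences in the intercept factor would indicate significant postintervention effects". On the slope: "Significant differences in slope factors would indicate that the groups follow different trajectories". It adds: "Tests of fixed effects for estimates of time-specific differences will be performed using appropriate contrasts".
- **Mediation and Moderation** describes a significant difference in a primary outcome as a significant treatment coefficient on either the intercept or the slope growth factor.
- **Sample Size Calculation and Power Analysis** states: "For the power calculation, we used 1 primary outcome, acceptability". It uses a logistic mixed model with five measurements including baseline, a first-order autoregressive correlation, 330 participants with 95% retention, and a baseline level of 85%. It claims 80% power at .05 for a time-averaged difference of 9 points (correlation 0.1) or 11 points (correlation 0.5).

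**The concern.** Two features of the power statement do not carry over to the analysis. First, the alpha: one of three unranked primary outcomes is powered at the full .05, while the analysis section spreads an overall .05 across tests. Second, the contrast: power is given for a difference averaged over time, but the outcomes are to be judged on intercept, slope or individual time points.

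The same data could therefore support different conclusions. A p-value of .01 passes Bonferroni over three tests (.05/3 = .0167) and fails over six (.05/6 = .0083). A p-value of .02 fails Bonferroni over three but passes Hochberg if all three p-values are at most .05. A reader also cannot take the 80% as the chance of success on acceptability under the plan as written.

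**Working it through.** **Inputs.** From the sample size section: 330 participants, 95% retention, baseline 85%, differences of 9 points (ρ = 0.1) and 11 points (ρ = 0.5), five measurements, α = .05, power 80%. Evaluable: 330 × 0.95 = 313.5, about 157 per arm. Assumed, because not stated: two-sided tests, and both directions of the difference (85 vs 94 or 76; 85 vs 96 or 74).

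**1. Reproducing the printed 80%.** For the mean of m measurements, the variance relative to one measurement is f = [1 + 2Σ(1 − k/m)ρ^k]/m, for k = 1 to m − 1. The effective n per arm is 157/f. Power is Φ[(d − z(1 − α/2)·SE0)/SE1], with SE0 the pooled and SE1 the unpooled standard error.
- ρ = 0.1, m = 5: f = 1.1728/5 = 0.2346, effective n = 669. Power for 9 points is 98.6% (85 vs 76) to above 99.9% (85 vs 94).
- ρ = 0.5, m = 5: f = 2.225/5 = 0.445, effective n = 353. Power for 11 points is 95.3% to 99.9%.

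The 80% does not reproduce. The printed pair of differences does appear with two measurements, 165 per arm and a downward difference (79.6% and 81.8%), but the section says five measurements.

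**2. Taking the 80% as printed and applying the promised correction.** A test with 80% power at two-sided .05 has noncentrality 1.960 + 0.842 = 2.802. Bonferroni power over K tests is Φ(2.802 − z(1 − .025/K)).

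| K | Level per test | Critical z | Power |
|---|---|---|---|
| 1 | .05 | 1.960 | 80% |
| 3 (the primary outcomes) | .0167 | 2.394 | 66% |
| 6 (three outcomes × intercept, slope) | .0083 | 2.638 | 56% |

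Hochberg over three outcomes, simulated with 200,000 draws and between-outcome correlations of 0, 0.5 and 0.8, gives about 66% if only acceptability has an effect and 75-77% if all three share it. Restoring 80% under Bonferroni over three needs 330 × (3.236/2.802)² = 330 × 1.334, or about 440 participants.

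**3. Correcting from the listed inputs instead.** At .05/3 the five-measurement time-averaged contrast keeps 96.2% to 99.9% for 9 points at ρ = 0.1, and 89.2% to 99.6% for 11 points at ρ = 0.5.

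**4. The contrast that is planned.** As an approximation, take a straight line over four equally spaced visits, centred at month 3, fitted by generalised least squares with ρ = 0.1 and no further random effects. The intercept's relative variance is 0.758, so effective n = 157/0.758 = 207. For a 9-point difference, power is about 64% to 85% at .05 and 47% to 73% at .05/3. The choice of contrast thus matters as much as the correction.

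**The case against.** The strongest reply is that this is a condensed article. It commits to an overall .05, and the list of tests and the choice of correction are commonly left to a statistical analysis plan that is not shown. That stands: an unlisted family is not in itself an error here. It does not remove the mismatch, because such a list cannot make an uncorrected .05 agree with a corrected one, or put the time-averaged difference among the tests this document names.

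A second reply is over-enrolment: 424 were enrolled against a target of 330. Scaling the printed 80% to 95% of 424 gives 78% at .05/3, which nearly restores it. Scaling to the 301 who completed 12 months gives 64%. So this depends on how many contribute data.

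Three stronger readings are tempting and not supported.
- *Uncontrolled false positives.* The abstract's phrase "using an α<.05 significance level" could suggest uncorrected testing. It condenses a section that goes on to promise correction, so error rates for uncorrected tests would describe a plan the protocol rejects.
- *An all-inclusive family.* Primary Outcomes, Secondary Outcomes and Table 2 do separate primary from secondary measures. One sentence makes comparisons at each follow-up depend on a slope difference, although another plans time-specific tests without that condition. Larger counts than the six intercept and slope tests are a reader's construction.
- *An underpowered trial.* Step 3 shows that this cannot be asserted: from the listed inputs the time-averaged contrast has ample power even after correction.

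**Conclusion.** The point holds as an inconsistency between the power statement and the analysis. The 80% applies to acceptability alone, at an uncorrected .05, on a contrast that the analysis sections do not name.

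Its size depends on what is accepted. If the printed 80% stands, power falls to about 66% under Bonferroni over three outcomes (66-77% under Hochberg) and about 56% over six tests. If the listed inputs stand, the time-averaged contrast is well powered, and the loss comes mainly from deciding on the intercept instead. All figures assume two-sided tests. The six-test family rests on the either/or wording in Mediation and Moderation. The mismatch itself depends on none of these numbers.

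**What to change.** 1. Name the between-arm time-averaged difference over months 3 to 12, the visits at which Primary Outcomes measures them, as the single deciding contrast for each primary outcome. Make the intercept, slope and time-specific tests supportive.
2. Limit the overall .05 in Statistical Analyses to the three primary outcomes, and place secondary outcomes and moderation tests outside that family.
3. Then choose one of two routes:
   - test acceptability first at the full .05, then appropriateness and feasibility in fixed sequence, each only if the one before is significant; or
   - use Hochberg over the three and restate the power at the corrected level.
4. In either case, redo the power statement on that contrast. With four visits and 157 per arm, f = 1.1605/4 = 0.290 at ρ = 0.1 and 2.0625/4 = 0.516 at ρ = 0.5. At .05/3 this gives 91% to 99% for 9 points and 84% to 99% for 11 points, respectively.

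**Cost.** No further participants or data are needed. Under the fixed sequence, appropriateness and feasibility carry no formal claim if acceptability fails. The Results section says data collection has ended and analysis is under way, so the change needs a dated record that it was made before between-arm results were seen. If that cannot be shown, the choice of contrast should be reported as made after the fact.

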### Planned Analytic Approach

Primary outcomes for the study include the acceptability, appropriateness, and feasibility of each intervention condition. In addition, we will examine behavioral health outcomes (sexual risk and protective behaviors and substance use) in both intervention conditions. Tests of fixed effects for estimates of time-specific differences will be performed using appropriate contrasts. Trend changes and their significance will be analyzed, driven by variance components (random effects). We will use growth curve modeling [75] to examine the effects of treatment on outcomes. Growth curve factors also account for the covariation of follow-up observations within participants. Data from 3-, 6-, 9-, and 12-month follow-up assessments will be modeled using latent growth factors using R statistical software [76] (version 4.4.0; R Foundation for Statistical Computing). Because the first nonbaseline time point in the latent growth curve will be the 3-month follow-up, significant differences in the intercept factor would indicate significant postintervention effects. Significant differences in slope factors would indicate that the groups follow different trajectories. When this is noted, potential group differences at each follow-up assessment will be evaluated by varying the location of the referent time point.

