### YMHP Intervention

The YMHP intervention consists of four 1-hour counseling sessions that use MI as a collaborative, goal-oriented approach of communication to discuss how participants manage sexual health and substance use in their daily lives. The goal of the YMHP counseling sessions is to explore these issues while supporting participants in making informed decisions for their health [36]. The sessions will be conducted by doctoral students trained in YMHP, holding master’s degrees in social work, and supervised by a licensed clinical social worker.

There is a wealth of evidence demonstrating the effectiveness of MI for behavioral change [49]. MI is rooted in the principles of engaging, focusing, evoking, and planning. The practice and implementation of MI use deep listening skills, effective reflections, and strategies for responding to resistance. Engaging involves building rapport and creating a sense of alliance through approaching participants with an attitude of curiosity, compassion, and understanding. Focusing involves exploring the participant’s view of their situation and selecting a target behavior for change. Although the main target behaviors are sexual health and substance use, understanding the participant’s priorities and goals is essential. Evoking is the act of finding out the participant’s own reasons for change and brainstorming how to reach those goals. Evoking can be achieved using open-ended questions and the Ask-Tell-Ask method [50]. Planning involves the creation of a course of action and the anticipation of obstacles. The transition into the planning stage should only be done when the participant is ready and willing to do so.

For this study, YMHP will be tailored and used with young adults across the SGM spectrum and will include gay and bisexual men as well as transgender women, transgender men, and gender nonbinary individuals who have sex with men, reflecting our study population.

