#### YMHP Scheduling (All Participants)

The interviewer will schedule the participant with their first YMHP session through Calendly, a scheduling website, with an interventionist who is not the baseline interviewer. The participant’s first session will be scheduled approximately 1 week after the onboarding and baseline survey (week 1). The interventionist and the participant will receive a calendar invite reminder for this session. Subsequent sessions are scheduled between the interventionist and the participant and will take place in week 2, month 1, and month 2 after onboarding. The scheduling process will take approximately 5 minutes.

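### The stated models and power calculation name no interventionist term, although the one primary scale both arms can answer rates counselling given by individual interventionists; adding it is a cheap, modest gain and a safeguard

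*Protocol article*

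**What the plan says.** **Delivery.** Both arms receive four YMHP sessions. Under YMHP Intervention the article states: "The sessions will be conducted by doctoral students trained in YMHP". Under YMHP Scheduling, the onboarding interviewer books the first session "with an interventionist who is not the baseline interviewer", and the interventionist and participant arrange the later ones between themselves. This reads as one interventionist per participant. Under Randomization, allocation precedes onboarding so that onboarding staff know the arm. No rule for spreading interventionists over arms is given.

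**Outcome.** Table 2 lists two sets of primary scales, one rating the SMS messages and one rating YMHP. The YMHP-only arm gets no messages, so only the YMHP scale can be compared between arms.

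**Analysis.** Planned Analytic Approach says: "Growth curve factors also account for the covariation of follow-up observations within participants". Mediation and Moderation also works with participant-level growth factors. The power calculation allows the repeated measurements of one person "for acceptability to be correlated via an autoregressive-1 structure". The Missing Data section provides for adjustment using baseline data only. No section on randomization, power or analysis mentions the interventionist.

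**The concern.** Ratings of counselling, and behaviour change after it, may depend on who gave it. Two things could follow from leaving the interventionist out:

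- If interventionists are spread similarly over the arms, their variance stays in the error term and precision is lost.
- If the mix differs systematically by arm, interventionist differences enter the arm contrast and the unadjusted test rejects too often.

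The rule for baseline imbalance would not catch the second case, because the interventionist is assigned after randomization and is not a baseline measurement. What is at stake is the only between-arm contrast on a shared primary scale, and the behavioural outcomes.

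**Working it through.** **The plan's own figure.** Inputs from Sample Size Calculation and Power Analysis: "With an initial sample size of 330 (to account for 95% retention), an autocorrelation of 0.1, and a baseline effectiveness of 85" percent; "we aimed to detect a minimum time-averaged difference of 9% in acceptability between any 2 conditions"; at autocorrelation 0.5, "the sample size was adjusted to detect a minimum difference of 11% between the 2 conditions"; "maintaining 80% power and an a priori α level of .05". Two-sided testing is assumed.

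- Completers per arm: 165 × 0.95 = 156.75.
- Variance factor for the mean of 5 AR(1) measurements: [1 + 2Σ(1 − k/5)ρᵏ]/5, which is 0.2346 at ρ = 0.1 and 0.445 at ρ = 0.5.
- Effective n per arm: 156.75/0.2346 = 668 and 156.75/0.445 = 352.
- Detectable difference from 85%: 5.1 points up or 5.9 down at ρ = 0.1; 6.8 up or 8.3 down at ρ = 0.5.

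The stated 9 and 11 points are not reproduced and look conservative. That is a separate matter, and nothing below rests on it.

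**Precision, with interventionists serving both arms in similar mix.** The ICC is an assumption. Adjustment multiplies the variance of the arm contrast by about (1 − ICC). At 80% power the standardized effect is 1.960 + 0.842 = 2.802, so power after adjustment is Φ(2.802/√(1 − ICC) − 1.960). The equivalent N is 330/(1 − ICC).

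| ICC | SE ratio √(1 − ICC) | Power after adjustment | Equivalent N |
|---|---|---|---|
| 0.01 | 0.995 | 80.4% | 333 |
| 0.02 | 0.990 | 80.8% | 337 |
| 0.05 | 0.975 | 82.0% | 347 |
| 0.10 | 0.949 | 84.0% | 367 |

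In simulation (n = 314, one continuous summary per participant, 6,000 replicates per setting), the unadjusted test under random mixing rejects in about 5% of null trials.

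**Type I error, if the mix differs systematically by arm.** Assume K interventionists in two equal halves, total variance 1 and n = 314. Let p₁ₖ and p₀ₖ be the share of each arm seen by interventionist k, S = Σpₖ² within an arm, and D = Σ(p₁ₖ − p₀ₖ)².

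- Variance the unadjusted test uses: e = (4/314)(1 − ICC·S).
- Actual variance: t = e + ICC·D.
- Type I error: 2[1 − Φ(1.96√(e/t))].

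For K = 8 and 70/30 versus 30/70, the shares are 0.175 and 0.075. So D = 8 × 0.1² = 0.08 and S = 4(0.175² + 0.075²) = 0.145.

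- ICC 0.05: e = 0.01265, t = 0.01665, type I error 8.8% (simulation 8.7%).
- ICC 0.10: e = 0.01255, t = 0.02055, type I error 12.6% (simulation 12.7%).

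For K = 8 and 60/40 versus 40/60, D = 8 × 0.05² = 0.02 and S = 4(0.15² + 0.10²) = 0.13. The formula gives 5.9% and 6.9% (simulation 6.2% and 6.8%).

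With K from 6 to 10 and ICC 0.05 to 0.10, the formula spans 5.7 to 7.5% for 60/40 and 8.0 to 15.0% for 70/30. In the simulations, interventionist fixed effects bring the error back to about 5%.

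**Could chance produce such splits?** The SE of the difference between two 50% shares with 157 per arm is √(2 × 0.25/157) = 5.6 points. The 60/40 case is a gap of 20 points (about 3.5 SE) and the 70/30 case a gap of 40 points (about 7 SE). Only sorting by arm would produce them. Imbalance of chance size is already covered by the unadjusted SE.

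**The case against.** **Openness of the model.** The quoted sentence says what growth factors account for; it does not exclude other terms. The same section mentions random effects without naming a grouping level, and Statistical Analyses leaves the choice of model open. A full analysis plan could include an interventionist term. This stands: the text shows that the term is not named, not that it is ruled out.

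**Likely size of the ICC.** YMHP is manualized, delivered under a licensed supervisor and audio recorded for fidelity, all of which favour a low ICC. This also stands, and it puts the expected gain towards the small end of the table.

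**The stronger reading.** A reader might infer that booking after allocation leaves the arms unbalanced in interventionists, so that the planned test rejects too often. The documents do not support that. Randomization is individual, all participants are booked by the same route, and nothing links the choice of interventionist to arm. Imbalance is possible, not shown.

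**Limits of the remedy.** Adjustment works only if interventionists serve both arms. If they were arm-specific, which the article neither says nor excludes, their effect could not be separated from arm, and fixed effects would not help. Simulated type I error of the unadjusted test would then be about 14%, 27% and 37% at ICC 0.02, 0.05 and 0.10 with eight interventionists. Adjustment is also not automatically safe if assignment depended on both arm and participant characteristics.

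What remains is that each place where the article describes dependence stops at the participant, and its covariate rule cannot reach the interventionist.

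**Conclusion.** The point holds as a low-cost improvement. Under a similar mix in both arms, the unadjusted test is valid at about 5%, and the price of omission is modest: 80% power could be about 80.4 to 82% at ICC 0.01 to 0.05 and about 84% at ICC 0.10. Inflated type I error is conditional on sorting by arm that the article permits but does not describe. The size rests on an assumed ICC, an assumed 6 to 10 interventionists, one continuous summary per participant and 314 completers. The article gives neither of the first two, nor whether each interventionist serves both arms. That last fact decides whether the issue is minor or serious, so the table by arm matters more than the power gain.

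**What to change.** 1. Report how many interventionists there were, and tabulate interventionist by arm.
2. Where interventionists serve both arms, add the interventionist scheduled at onboarding, as a fixed effect or random intercept, to the between-arm models for YMHP acceptability, appropriateness and feasibility and for the behavioural outcomes. Using the scheduled interventionist classifies all participants, including those who attended no session.
3. If any interventionist served one arm only, state that this person's effect cannot be separated from arm.
4. If the table shows marked imbalance, say how interventionists came to be assigned, and show results with and without the term.

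The cost is a few degrees of freedom and one table. The interventionist should be recoverable from the scheduling records. Results are not yet published, so the term can still be added, with its date recorded.
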